All subjects will be randomly assigned 1:1, with the use of a numeric sequence standard procedure, into treated-with-PEA (composed of 600 mg PEA in capsules; orally, two times per day) or placebo (capsules; orally, two times per day) arms. Both MCI subjects and controls will be divided into two arms: for the MCI group, 25 subjects will be randomized in the PEA arm and 25 subjects in the placebo arm; for control group, 15 controls will be randomized in the PEA arm and 15 in the placebo arm. At the time of enrollment, all participants will be assigned to one of the two main groups (MCI or HC), then they will be assigned a sequential number. Following the random generation sequencing program (www.randomizer.org), each participant will be automatically assigned to one of the two treatment conditions without the direct involvement of any researcher, in order to avoid any personal bias.

Treatment will last for 12 months (T1), followed by a 6-month observational period (T2). All evaluations performed at T0 will be reassessed at T1 and T2.

Aims 2 and 3:

In addition to the above, blood and urine specimens will be obtained from all participants at T0, T1 and T2. All samples will be immediately stored and then analyzed for measuring PEA, its endocannabinoid congeners and other biological markers.

The planned duration of the study is 36 months considering subject enrollment, clinical evaluation, sample collection, treatment duration, post-treatment follow-up, processing, interpretation and result disclosure.

Figure 1 shows the study flowchart.

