#### 2.3.2. Biochemical Analyses

Biological samples from subjects at T0, T1 and T2 will be aliquoted, stored at −80 °C until the evaluation of the following biochemical parameters:Apolipoprotein (apo) E genotyping: ApoE genotype of each participant will be determined via PCR, according to standard procedures. Humans have three versions of the APOE gene: ε2, ε3 and ε4 alleles. ApoE genotyping can help estimate a patient’s risk of converting from MCI to AD. In fact, in precedent studies, the epsilon4 allele of apolipoprotein E was considered as the major genetic risk factor for AD onset [27] and conversion to dementia in MCI patients [28].Central and peripheral inflammation: Selected inflammatory markers, specifically altered in MCI and possibly providing predictive information in AD progression, namely, C-reactive protein, interleukin (IL)-6, IL-8, IL-10, monocyte chemotactic protein-1, macrophage inflammatory protein-1beta and soluble triggering receptor expressed on myeloid cells 2, will be evaluated via ELISA and/or the Luminex platform.Amyloid-β, tau and neurofilament light chain: To monitor disease progression and treatment response, neurofilament light-chain protein, Aβ42, total and phosphorylated tau will be quantified via ELISA or using the multiplex Luminex platform.Oxidative stress: The effects of PEA treatment on oxidative/nitrosative stress that occurs at an early stage in AD will be assessed by measuring the presence of 3-nitrotyrosine and 4-hydroxynonenal (two end products of peroxynitrite), through ELISA [29].PEA, AEA and their main catabolic enzymes: The levels of PEA and AEA will be assessed via state-of-the-art liquid chromatography/mass spectrometry. In parallel, enzymatic activity of FAAH and NAAA [5] will be measured via radiometric assays.

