## 3. Statistics and Outcomes

### 3.1. Data Analysis

The sample size needed to achieve significant differences was determined based on an a priori power analysis, using the software G*Power 3.1 (Version 3.1.9.4; Program written by Franz Faul, Universatat Kiel, Germany) [30] and published data on changes of Aβ42 levels in CSF of MCI vs. CTRL [31]. For a two-sample *t*-test, accepting a probability of type I error of 5% and a probability of type II error of 20%, required the following sample size for the outcome: Aβ 42 (ngl/mL), delta 42, SD 52, results to be N = 25/group. Based on the above, we propose to enroll 30 subjects per group, with the intent of having 23–25 finishers per group to account for potential dropouts. For the aims of our study, we plan to also enroll 30 control subjects that will be equally distributed within the PEA and placebo arms.

Experimental data will be analyzed using Student’s *t*-test or one- and two-way analyses of variance, followed by Bonferroni post hoc test for multiple comparisons. Differences between the groups will be considered statistically significant at values of *p* < 0.05. Pairwise correlation between variables will be assessed via Pearson’s test and confirmed using Spearman’s rank. Significant outliers will be excluded performing the Grubbs’ test, again, with statistically significant values considered at *p* < 0.05.

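### Values that fail Grubbs' test are excluded with no requirement of a documented error; if the inflammatory markers are right-skewed this deletes genuine data, and the false-positive rate then runs from about 5% to 17% depending on how the rule is applied

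*Protocol article*

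**What the plan says.** Section 3.1 (Data Analysis) of the protocol article fixes the rule: "Significant outliers will be excluded performing the Grubbs’ test", "again, with statistically significant values considered at" p < 0.05. The only criterion for removal is statistical significance. The same section compares groups by Student's t-test "or one- and two-way analyses of variance, followed by Bonferroni post hoc test for multiple comparisons".

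Section 2.3.2 lists the inflammatory markers, among them "C-reactive protein, interleukin (IL)-6, IL-8, IL-10, monocyte chemotactic protein-1, macrophage inflammatory protein-1beta" and soluble TREM2, and does not describe their distributions. Section 3.2 makes a fall in neuroinflammation markers part of the primary outcome. Section 2.1 gives the arm sizes: in the MCI group "25 subjects will be randomized in the PEA arm and 25 subjects in the placebo arm", and in the control group "15 controls will be randomized in the PEA arm and 15 in the placebo arm".

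The article does not say whether Grubbs' test is run per arm or on pooled arms, once or repeatedly, or on raw values, logged values or changes.

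**The concern.** Grubbs' test asks whether the most extreme value is compatible with a normal sample. For a positive, right-skewed concentration, an ordinary high reading can fail. The rule would then remove real patients with high inflammation from a comparison whose purpose is to measure inflammation, and different patients would be missing for each marker.

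Two things are at stake. If each arm is trimmed separately, its upper tail is cut at its own limit. The remaining SD is then too small, so the t-test rejects too often. If the arms are pooled, most deletions fall in the arm with the higher values, and part of the treatment contrast goes with them.

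**Working it through.** **The plan's own figure.** Section 3.1 gives "delta 42, SD 52, results to be N = 25/group". The normal approximation is n = 2 × (1.960 + 0.842)² × (52/42)² = 2 × 7.85 × 1.533 ≈ 24.1, rounded up to 25. The noncentral t gives 25.06, and 79.9% power at 25 per group. The figure reproduces and is not affected by this point. The standardised effect is 42/52 = 0.81.

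**Inputs.**
- From the document: exclusion by Grubbs at 0.05, then a t-test at 0.05; 25 per MCI arm and 15 per control arm.
- Assumed: both tests two-sided; markers log-normal with log-SD 0.5–1.0; for change scores, log-SD 0.5–1.5 and a correlation of 0.6 between visits.

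**Rule simulated.** G = max|x − mean|/SD. The value is excluded if G > ((n − 1)/√n) × √(t²/(n − 2 + t²)), where t is the 1 − 0.05/(2n) quantile with n − 2 degrees of freedom. The limit is 2.82 for n = 25 and 3.13 for n = 50.

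**Check on normal data.** Two arms each tested at 5% lose a valid value with probability 1 − 0.95² = 9.75%. Simulation gives 9.4%, and the following t-test rejects in 5.4% of null trials.

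**Null rejection rate, 25 per arm, no true effect (40,000 trials per setting, nominal 5%).**

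| Application of Grubbs to raw values | log-SD 0.5 | 0.75 | 1.0 |
|---|---|---|---|
| No exclusion | 4.7% | 4.5% | 4.0% |
| Pooled arms, once | 4.9% | 5.0% | 4.7% |
| Pooled arms, repeated | 5.1% | 5.2% | 5.1% |
| Per arm, once | 7.6% | 8.6% | 8.4% |
| Per arm, repeated until clean | 9.8% | 13.7% | 17.5% |
| Comparisons losing at least one genuine value, per arm | 62% | 82% | 92% |

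Separate runs agree within simulation error, which is why the summary ranges are 4–6%, 8–9%, 10–17% and 61–92%.

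- Mean loss at log-SD 1.0, per arm, repeated: 2.7 of 50 values (5.4%). A single pass removes about 2.9%.
- Control group, 15 per arm, log-SD 1.0: 13.8% per arm repeated, 8.9% per arm once, 4.6–5.0% pooled.
- Change scores, per arm, 25 per arm: 5.0–7.5%.
- Logged values with nothing removed: 4.9%. Grubbs per arm on logged values: 5.4%.

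**Pooled use when there is a true effect.** With a log-scale difference of 0.81 SD and pooled, repeated Grubbs, about 85–89% of deleted values come from the higher arm. The raw mean difference shrinks by about 16%, 30% and 46% at log-SD 0.5, 0.75 and 1.0. Power is about 73%, 65% and 60%, against 79–81% for a t-test on logged values with nothing removed.

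**Where the power gap comes from.** A further run (20,000 trials per setting) gives the raw-scale t-test with nothing removed about 75%, 69% and 61% power. Most of the gap to 80% therefore comes from analysing skewed values untransformed, and only a few points come from the exclusion. The harm specific to pooled exclusion is the shrunken estimate.

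**The case against.** The strongest counter-case is that the size of the problem rests on conditions the article does not state. A reader might infer that the rule roughly triples the false-positive rate. That needs Grubbs run separately in each arm, repeated until clean, on untransformed values, with a log-SD of about 0.75–1.0. The article states none of these. The plural (outliers) is as consistent with one pass per marker as with repetition. Pooled testing gives no inflation, a single pass per arm at most about 1.8 times nominal (8.9% with 15 per arm), and change scores at most about 1.5 times. This objection stands against the tripling claim.

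It also stands that skewness is an assumption, that the average number of values lost is small, and that raw data with no exclusion already hold the 5% level. Log transformation is therefore not needed to protect type I error; its benefit is power.

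A further objection is that a journal article leaves transformations and sensitivity analyses to the full protocol or analysis plan. That is right, and their absence is not the point here. The exclusion rule, however, is stated, together with its test and threshold, and it removes values for being extreme. The Spearman check in Section 3.1 applies to correlations and does not cover the group comparisons.

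**Conclusion.** The concern holds in a bounded form. Section 3.1 removes data on statistical significance alone, using a test that assumes normality, from markers that belong to the primary outcome. If those markers are log-normal with log-SD 0.5–1.0, per-arm use deletes genuine values in most comparisons. The false-positive rate then depends on the application: near nominal when pooled, less than double for one pass per arm, and two to three and a half times nominal when repeated per arm (9.8/5 ≈ 2.0; 17.5/5 = 3.5). Pooling protects the error rate but biases the raw difference towards zero.

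The documents do not support a single figure for the inflation, because they fix neither the application nor the distributions. For near-normal markers the effect on type I error is negligible. The simulations cover the two-arm t-test; the ANOVA was not simulated.

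**What to change.** Replace the outlier sentence in Section 3.1 with:

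*All valid measurements are analysed. Grubbs' test is used, blinded to arm, only to prompt an assay or data-entry check, and a value is removed only for an error documented before unblinding.*

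Add that skewed biomarker concentrations are analysed on the log scale, and that any analysis with Grubbs exclusions is reported only as a sensitivity analysis, stating whether the test is run per arm or pooled and once or repeatedly.

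The cost is analysis wording and a few assay rechecks. Sample size and trial conduct do not change.

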### 3.2. Outcomes

For the primary outcome of the study, we expect that PEA administration will decrease the levels of neuroinflammation markers and improve cognitive performance in MCI subjects.

Moreover, for the secondary outcome, we expect to find a reduced conversion from MCI to AD in subjects treated with prolonged PEA administration compared to those within the placebo arm.

For the last outcome, we will also identify the PEA-induced biochemical profile of selected AD targets and its correlation with MCI subjects’ cognitive performance, gaining new insight into biological mechanisms underlying PEA effects on amyloidosis-induced pathology.

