### 2.3. Assessment Procedures

#### 2.3.1. Humans Cognitive, Behavioral and Functional Disability Assessment

The RBANS battery [23] will be used for cognitive assessment. This neuropsychological battery measures cognitive decline, even in very mild dementia, or improvement across different domains: Immediate Memory, Visuospatial/Constructional Abilities, Language, Attention, Delayed Memory.HADS [24] will be used for behavioral assessment. It is useful in identifying the anxiety and depression levels of participants.IADL [25] is an appropriate instrument to assess independent living skills at a functional level.The DT [26] protocol assesses the cognitive–motor efficiency when simultaneously performing a cognitive and a motor task. It seems to be a reliable tool even in pre-dementia stages and consists of performing three 2 min tasks, two neutrals (motor task, cognitive task) and the other one with the concurrent tasks.

All these evaluations will be repeated after one-year PEA/placebo treatment and at the follow-up visit.

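### The primary outcome is a family of about 8 to 12 variables with no success rule, and the one stated correction (Bonferroni post hoc after ANOVA) does not act across outcomes and has no defined scope

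*Protocol article*

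**What the plan says.** - **Primary outcome (section 3.2).** "we expect that PEA administration will decrease the levels of neuroinflammation markers and improve cognitive performance in MCI subjects". The section gives no variable, no visit, and no statement of whether one, some or all components must succeed. Aim 1 in section 2.1 refers to one year of treatment for the clinical scores, but section 3.2 does not carry this over.
- **Markers (section 2.3.2).** Seven inflammatory markers are listed. Aβ42 appears under a separate heading, with tau and neurofilament light chain.
- **Cognition (section 2.3.1).** RBANS is the cognitive battery, covering "Immediate Memory, Visuospatial/Constructional Abilities, Language, Attention, Delayed Memory". The dual task is assessed as well.
- **Analysis (section 3.1).** Student's t-test is offered as an alternative to one- or two-way ANOVA, the latter "followed by Bonferroni post hoc test for multiple comparisons. Differences between the groups will be considered statistically significant at values of" p < 0.05. The comparisons that Bonferroni covers are not defined.
- **Sample size (section 3.1).** One two-sample t-test on Aβ42: "delta 42, SD 52, results to be N = 25/group".
- **Allocation (section 2.1).** "for the MCI group, 25 subjects will be randomized in the PEA arm and 25 subjects in the placebo arm"; controls are split 15 and 15. This makes four cells. Aim 1 plans the PEA-placebo comparison in both MCI subjects and controls.

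**The concern.** Two matters meet here.

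1. **Error across the primary variables.** The primary claim rests on several markers and on cognition, all judged at the same threshold. A post hoc test that compares cells within one ANOVA does nothing about picking the significant result from several ANOVAs. Without a success rule, the trial could be reported as positive on whichever component reached p < 0.05.
2. **Scope of the Bonferroni step.** The contrast that answers the primary question is PEA versus placebo in MCI subjects. The article does not say whether this is tested as a planned contrast at 5% or enters the post hoc family at a smaller level. The sample size was set for a single test at 5%, so it allows for neither form of multiplicity.

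**Working it through.** **Reproducing the plan's figure.** Inputs from section 3.1: delta 42, SD 52, type I error 5%, power 80%. Sidedness is not stated. Two-sided is assumed because it reproduces N; one-sided would give 19 to 20 per group.

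- d = 42/52 = 0.808.
- Normal approximation: n = 2(1.960 + 0.842)²/0.808² = 24.06, rounded up to 25 per group.
- Noncentral t: 25 per group gives 79.9% power; 26 is the first n above 80%.

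The stated 25 per group is reproduced.

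**Counting the primary family.** Seven markers plus one RBANS summary = 8. Seven markers plus five RBANS domains = 12. The dual task or a second visit would add to this.

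**Chance of at least one false positive, each test at 0.05, any one counting as success.** Under independence the chance is 1 − 0.95^k:

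- k = 7: 30.2%
- k = 8: 33.7%
- k = 12: 46.0%

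With correlated test statistics (simulation of equicorrelated normal statistics, 200,000 draws):

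| Common correlation | 8 variables, either direction | 8, favouring PEA only | 12 variables, either direction | 12, favouring PEA only |
|---|---|---|---|---|
| 0.3 | 30% | 15% | 40% | 20% |
| 0.5 | 25% | 12% | 32% | 16% |
| 0.7 | 19% | 10% | 23% | 12% |

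The reference values for one test are 5% in either direction and 2.5% favouring PEA.

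**If success needs at least one marker and at least one RBANS domain.** With no true effect anywhere and independence:

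- Either direction: (1 − 0.95^7)(1 − 0.95^5) = 0.302 × 0.226 = 6.8%.
- Favouring PEA: (1 − 0.975^7)(1 − 0.975^5) = 0.162 × 0.119 = 1.9%.

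If cognition truly improves and no marker changes, the cognitive part no longer restrains the claim. Error in the marker part can then approach 30.2% (either direction) or 16.2% (favouring PEA).

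**Power of the MCI PEA-placebo contrast if Bonferroni applies to it.** Inputs: d = 0.808, 25 per arm, four cells, 80 subjects, so pooled df = 80 − 4 = 76. Noncentrality = 0.808 × √(25 × 25/50) = 2.86.

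| Bonferroni family | Level | Power |
|---|---|---|
| none, plain t-test (df 48) | 0.05 | 79.9% |
| none, four-cell ANOVA | 0.05 | 80.5% |
| two contrasts (MCI and controls) | 0.025 | 71.5% |
| all six pairwise cell comparisons | 0.0083 | 56.0% |

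At 23 finishers per MCI arm, the lower end of the range the plan intends, the six-comparison figure is 51.4%. Keeping 80% power over six comparisons would need 38 to 39 per arm.

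**The case against.** **The power loss is not in the text.** A reader might infer that the plan tests the main contrast at 0.05/6. It does not say so. Section 3.1 permits a t-test with no penalty, the Bonferroni family is undefined, and Aim 1 makes a family of two contrasts just as possible. This stands: the loss is conditional, and the fault is that the scope is left open.

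**The effect size belongs to another variable.** Delta 42 and SD 52 are for Aβ42 in MCI versus controls, and Aβ42 is not among the listed inflammatory markers. The article gives no effect size for the markers or RBANS. This stands too: the power figures show what the correction costs under the plan's own assumptions, not the power for the primary outcome.

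**The false-positive figures need a success rule that the plan does not state.** Correct, and the five RBANS domains are described as what the battery measures, not as five separate primary tests. Hence the range from 8 to 12 variables, the correlated and directional figures, and the stricter reading in which both parts must succeed. That stricter reading largely removes the inflation when nothing works, but not within the marker part when cognition improves.

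**Blood and urine.** A reader might double the marker count to 14 and obtain 1 − 0.95^19 = 62% with the five domains. The documents do not support this. Aim 2 mentions both fluids for markers collectively, section 2.3.2 does not say that each marker is assayed in both, and independence of one marker across two fluids is implausible.

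**It could be left to an analysis plan.** The exact post hoc family could be. But the article itself fixes a plural primary outcome, a threshold and a correction, and the three do not fit together. Naming the primary variable belongs in the protocol.

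**Conclusion.** The point holds in two parts of different strength.

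- **Firm.** The primary outcome is a set of variables without a named variable, time point or success rule, and the Bonferroni step as ordinarily used does not control error across them. If any one result suffices, the chance of a false positive somewhere is about 34% (8 variables) to 46% (12) under independence. For 12 variables it is 40% to 23% over correlations of 0.3 to 0.7, and 20% to 12% counting only results favouring PEA. It would go too far to say that a false-positive primary result is more likely than not.
- **Conditional.** If the ANOVA route is taken and the MCI contrast falls inside the Bonferroni family, power under d = 0.808 and 25 per arm falls from about 80% to 71.5% (two contrasts) or 56.0% (six). By t-test there is no loss.

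The protocol should be changed on this point before data are analysed.

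**What to change.** 1. Name one primary variable. It could be one prespecified RBANS summary score or another variable the sponsor chooses; the article mentions no RBANS total score, so the choice is the sponsor's.
2. Test the PEA-placebo difference in MCI subjects at T1 once, at two-sided 5%, as a planned contrast outside the post hoc correction.
3. If one cognitive variable and one marker are both kept as primary, state whether both must succeed (each at 5%) or either may (Holm).
4. Make the seven inflammatory markers key secondary outcomes with Holm across them.
5. Label the remaining scores, fluids, visits and control-group comparisons exploratory.

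**Cost.** This is mainly wording, and some markers and scores can no longer carry a confirmatory claim. With one primary variable the error is 5% and 25 per arm can stay, with about 80% power if the Aβ42 effect size carries over. On the same assumption:

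- Two primary variables where either may succeed, planned at 0.025 each, need 30 to 31 per arm; at 25 per arm the power for each at that level is about 71%.
- Requiring both at 5% gives joint power of 0.799 × 0.799 = 64% if they are independent.
- Bonferroni over all 12 variables would need 43 to 45 per arm.

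The sponsor should give an effect size for the variable it chooses, since the article has none.

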## 4. Discussion and Conclusions

New drugs able to act on pathogenic mechanisms of AD may cover therapeutic areas where there are few or no treatments. To date, PEA is clinically used for conditions other than AD, and its safety and tolerability have been well-documented. Our proposal may have a significant impact on individual health and economic and social burdens. The possibility of a new therapeutic strategy in the early phases of the disease could provide therapies with the potential to alleviate the symptoms and also modify the disease progression. The quality of life in elderly and healthy aging populations has a remarkable societal impact. Today, approximately 50 million people worldwide live with dementia and this number is expected to increase to about 152 million by 2050; hence, AD may be considered an epidemic with an impact not only on patients and their families, but also on the worldwide healthcare system.

This project will open the gates to the use of substances, devoid of harmful effects, able to act on a specific mechanism that causes cellular damage typical of AD and, therefore, ways to delay the possible progression of MCI subjects to the AD stage.

